## Abstract

**Background::**

Lesions of herpes labialis are caused by the herpes simplex virus type 1 and cause pain and aesthetic compromise. It is characterized by the formation of small vesicles that coalesce and rupture forming extremely painful ulcers, that evolve to crusts, dry desquamations until their complete remission. Currently the treatment of these lesions is done with acyclovir. Although it diminishes the symptomatology, it causes viral resistance and does not prevent the recurrence of the lesions. It is known that antimicrobial photodynamic therapy (aPDT) has numerous advantages, among them: the reduction of the time of remission, and does not cause resistance. This protocol will determine the effectiveness of PDT in lesions of herpes labialis.

**Materials and methods::**

A total of 30 patients with herpes labialis in the prodromal stage of vesicles, ulcers, and crusts will be selected to participate in the study and randomized into 2 groups: G1 control and G2 experimental. After signing Research Ethics Committee and TA, patients in group G1 will undergo the standard gold treatment for herpes labialis with acyclovir and simulated PDT treatment. Patients in the experimental G2 group will be treated simulating the gold standard treatment of herpes labialis (placebo) and PDT. In all patients, saliva samples will be collected for analysis of cytokines, and will be performed exfoliative cytology in the lesions. The pain will be assessed through a pain scale and a questionnaire of quality of life related to oral health (OHIP-14) will be given to them. Patients will continue to be followed up after 7 days, 1 month, 3 months, and 6 months; if there is a recurrence of the lesion, they will contact the researchers.

Clinical registration: clinicaltrials.gov - NCT 04037475. Registered on July 2019.

## Introduction

1

The prevalence of herpes labialis increases gradually in childhood, reaching 70% to 80% of adults worldwide.^[1–3]^ Recurrence of herpes occurs in 20% to 40% of the world's population.^[4]^ Herpes labialis are an infectious disease caused by the herpes simplex virus (HSV). HSV type 1 (HSV-1) and HSV-2 subtypes affect the skin and mucous membranes, but the HSV-1 subtype affects the orofacial region more. Recurrent herpes labialis can also be known as “fever blisters” or “cold sores.”^[5]^ Initial primary infections are usually more severe than recurrent ones, since the patient does not have acquired immunity.^[6]^ Herpetic gingivostomatitis usually occurs in young children characterized by painful oro-labial vesicles that coalesce and rupture forming ulcers, lasting between 10 and 14 days, accompanied by fever, malaise, fatigue, pain muscle, and dehydration.^[6–9]^

Clinically, the recurrence of the lesions goes through stages: prodromal, redness, papule, gallbladder, ulcer, crust, dry scaling, and remission of the lesion. Many of these stages may be short or imperceptible.^[6,10,11]^ It is a self-limiting, painful disease that generates discomfort, social restraint, and aesthetic compromise. In immunocompromised patients, recurrent lesions are more aggressive and take longer to heal.^[12,13]^ Because of these factors, associated with several recurrences, studies are important for other alternatives to treat herpes labialis, aiming to a fast resolution of the lesions, with less time of recurrence, without undesirable side effects.

Aciclovir is the most widely used medication to prevent or suppress HSV-1.^[10,14]^ Continuous use of these drugs may develop a high viral resistance.^[7,10]^ Antiviral medications are most effective when the patient is still in the prodromal phase. Aciclovir is effective in reducing the duration and symptoms of infection, but the optimal dose is still unknown.^[9]^ Although acyclovir decreases the duration of symptoms, it does not prevent recurrence.^[15–17]^ In view of the resistance that antiviral treatment can cause and the recurrence of the lesion, some alternative treatments have been studied, such as antimicrobial photodynamic therapy (PDT), which is a good option.^[18]^

The PDT is a therapeutic option in many fields of medicine.^[19]^ It is selective and noninvasive, also indicated for transplant and oncology patients.^[15]^ It consists of the combination of a chromophore agent, such as methylene blue, at a certain concentration, associated with monochromatic laser light at a given wavelength.^[20]^ The photosensitizer (methylene blue) absorbs visible laser light at a suitable wavelength (660 nm) from the ground state to the singlet state, which has a short shelf life. From there, the photosensitizer can lose energy through nonradioactive, radioactive (phosphorescence) processes, or generate reactive oxygen species (ROS) through 2 mechanisms: either by electron transfer, forming free radicals (type I reactions), or through the transfer of energy to molecular oxygen forming singlet oxygen (type II reactions).^[21]^ The lesions of herpes labialis are recurrent in some patients, causing pain, aesthetic commitment, and absenteeism in the work. Your complete remission lasts until 15 days. Treatment with acyclovir decreases painful symptoms; however, it causes viral resistance and does not prevent recurrence of the lesions. It is known that antimicrobial PDT (aPDT) has numerous advantages among them the reduction of the time of remission and, moreover, does not cause resistance; although there are still no well-designed clinical studies that prove its effectiveness, there are only case reports. Therefore, the objective of this study will be to evaluate whether PDT is able to reduce the healing time of these lesions and decrease their recurrence.

## Methods

2

This is a single-center randomized, double-blind, controlled, prospective trial consistent with the criteria for designing a clinical SPIRIT statement. The project will be submitted to the Research Ethics Committee of Universidade Nove de Julho (UNINOVE). After verbal and written explanation of the study, participants who agree to participate in the study will sign the informed consent form (ICF) and the term of consent (TC) for children under 12 to 18 years of age ([name]). The study will be conducted in accordance with the Declaration of Helsinki. The project will be registered at www.clinicaltrial.gov. Project receive grant from Brazilian National Council for Scientific and Technological Development - CNPq #165189/2019-3 (CNPq, Portuguese: Conselho Nacional de Desenvolvimento Científico e Tecnológico). Patients will be invited to attend the Dental Clinic of the University of Nove de Julho (UNINOVE), at city of São Paulo, Brazil, from January 2020 to August 2021 for PDT treatment and evaluation. The experimental design will consist of 2 groups. The sample will be composed of healthy patients who have herpes lesions in the vesicle or crust stage. The total time for lesion remission, ballooning cell verification, virus quantification at the site of injury, and saliva will be assessed. Samples (HSV secretion) will be collected at the injury site and saliva for the quantification of inflammatory cytokines. Pain, temperature, and recurrence of the lesion will be assessed at a 1-year follow-up. The OHIP-14 questionnaire will also be used to measure quality of life related to oral health. Patients will return in 3 days (T1), 7 days (T2), 30 days (T3), 6 months (T4), and 1 year (T5) for reevaluation. Every time there is recurrence of the lesion, the clinic will be invited for collection and verification of the lesion site (recurrence in the same place, it will be noted in the labial diagram by sextant) (Fig. 1).

**Figure 1 F1:**
[figure not shown]
Flowchart. REC = Research Ethics Committee, ICF = Informed Consent Form, OHIP-14 = Oral Health Impact Profile Questionnaire, VHS = virus Herpes Simplex, PDT = photodynamic therapy.

### Sample size calculation

2.1

The sample was calculated using standard error type 1 of 0.2 and 95% confidence level as indicated in the literature.^[22–27]^ The calculation is consistent, equivalence tests in nonparametric models of survival (Kaplan and Meier, 1958). The survival function, at a given time *t*, can be estimated from observed survival times, relative to the proportion of individuals who survived beyond time *t*. In our case, time *t* is defined as the treatment date, and survival is estimated in days until recovery of the patient. Based on the survival analysis methodology, a sample of 24 participants (12 per group) was calculated. The estimation of differences between groups will be done based on the Kaplan–Meier estimator or limit product estimator.

### Evaluators calibration and training

2.2

For calibration there will be only 1 examiner ([name]) who will do 5 pain assessments with visual analogic scale (VAS), which will not be part of the study. There will be 2 evaluations per patient (with a 30-minute interval between them) to check for intraexaminer agreement. The intraclass correlation coefficient (ICC) will be calculated to evaluation will be performed with a 0 to 10-cm millimeter ruler by a researcher that will not be involved in the treatment of the patients. Calibration as described (ICC) shall be performed for all measurable data.

This same examiner will be trained for all evaluations that do not allow quantitative and qualitative measurements such as: collection of secretion and saliva. These procedures are important to maximize the reproducibility of evaluations.

### Sample description

2.3

The sample will be composed of healthy patients aged 15 to 60 years who have herpes lesions in the prodromal stage, vesicles, ulcers, and crusts.

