### Inclusion and exclusion criteria

2.4

Patients of both sex, with no predilection for race or socioeconomic status, would be included (negative medical history).

Patients with herpes infection in the dry desquamation stage will be excluded. Participants in continuous use of nonsteroidal anti-inflammatory drugs and continued corticosteroid therapy ^[28]^ for <1 week, diabetic participants, smokers who need immunosuppressants, pregnant women and/or nursing mothers, human immunodeficiency virus positive, and hepatitis B or C will be also excluded.

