### Anamnesis

2.8

Anamnesis will be performed in both groups. In addition to general patient health questions, demographic data (age, gender, marital status, occupation, educational level, living conditions, and salary), medical history data (primary complaint, current illness status, medical history, dental history, and medications) and will be asked when was the first infection and how many infections occurred within 1 year. The patient will be asked if there is a relationship between stress/begin of the injury and anxiety/begin of the injury.

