### Statistical analysis

2.14

Statistical analysis will be performed using only the data obtained from the patients who complete the study. The Kolmogorov–Smirnov test will be applied before the analysis of the normality of each parameter. The *t* test will be used to compare all means. All tests will be performed using Graphpad Prism 5 (Graphpad Software, San Diego, CA). Data will be presented on average and ±standard deviation. The level of significance will be set at *P* < .05.

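### Healing time runs from treatment while lesions enter at successive stages, and neither the randomisation nor the stated comparison uses stage, which costs precision in a trial of 12 to 15 per arm

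*Protocol article*

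**What the plan says.** **Eligible stages.** Section 2.3 (Sample description) enrols "healthy patients aged 15 to 60 years who have herpes lesions in the prodromal stage, vesicles, ulcers, and crusts". The opening of section 2 (Methods) is narrower: "The sample will be composed of healthy patients who have herpes lesions in the vesicle or crust stage". Section 2.4 removes only one stage: "Patients with herpes infection in the dry desquamation stage will be excluded".

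**Stages as a sequence.** The Introduction states: "Clinically, the recurrence of the lesions goes through stages". It lists them in order from prodrome to remission, and later gives up to 15 days for complete remission.

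**Time origin.** The primary variable is resolution time in days (section 2.12). Section 2.1 says that time *t* "is defined as the treatment date, and survival is estimated in days until recovery of the patient".

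**Randomisation.** Section 2.5 allocates 1:1 in five blocks of six, with no stratification factor.

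**Comparison.** Section 2.14 says that a *t* "test will be used to compare all means", at P < .05. Section 2.1 bases the group difference on the Kaplan–Meier estimator. Neither names a stratum or a covariate.

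**Baseline data.** Section 2.12 takes VAS, OHIP-14, HSV-1 and cytokines at T0. Section 2.8 asks patients "how many infections occurred within 1 year".

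**The concern.** If the stages follow one another within an episode and the clock starts at treatment, days to resolution contain a component fixed before randomisation: how far the lesion had already progressed. That component adds between-patient variance unrelated to treatment. With 12 to 15 patients per arm it can lower power noticeably, and the arms can differ in stage mix by chance.

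Stage has to be observed before treatment in any case. It decides eligibility (section 2.4) and whether the vesicle step in section 2.10 applies. Leaving it out of the comparison discards prognostic information that costs almost nothing to use.

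The two lists of eligible stages also leave the spread of stages unclear. Even the narrower list mixes an early stage with a late one.

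**Working it through.** **The plan's own figures.** The 24 patients (12 per group) cannot be reproduced, because section 2.1 gives no effect size, SD, hazard ratio or margin. Solving backwards at two-sided 5% and 80% power:
- two means: standardised difference = (1.960 + 0.842) × √(2/12) = 1.14
- Schoenfeld with 24 events: healing-rate ratio = exp[(1.960 + 0.842) × 2/√24] = 3.14

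The dropout step does reproduce: 24/(1 − 0.20) = 30, or 15 per group. The plan therefore supplies no target effect against which a stage shift could be measured.

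**Assumptions (none is in the article).** Mean remaining days for prodrome/vesicle/ulcer/crust are 10/8/6/4, with 9/8/7/5 as a flatter alternative. The four stages are equally frequent, the within-stage SD is 2 days, and the true benefit is 2.5 days.

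**Variance due to stage.**
- 10/8/6/4: mean 7; variance (9 + 1 + 1 + 9)/4 = 5.0; total 5 + 4 = 9, SD 3.0; stage share 5/9 = 56%.
- 9/8/7/5: mean 7.25; variance 8.75/4 = 2.19; total 6.19, SD 2.49; stage share 35%.

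**Chance imbalance under 10/8/6/4.** The SD of the stage-driven difference between arms is √(5 × 2/12) = 0.91 day at 12 per arm and √(5 × 2/15) = 0.82 day at 15. By simulation it exceeds 1 day, in either direction, in about 24% of trials at 12 per arm. It exceeds 2 days in about 2% and 2.5 days in about 0.4%.

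**Power by normal approximation, 12 per arm.** Power = Φ(2.5/(SD × √(2/12)) − 1.96).
- 10/8/6/4, stage ignored: SD 3.0, Φ(2.04 − 1.96) = 53%.
- 10/8/6/4, stage in two levels (prodrome/vesicle against ulcer/crust, means 9 and 5): this removes variance 4 and leaves 5, SD 2.24, Φ(2.74 − 1.96) = 78%.
- 9/8/7/5, stage ignored: SD 2.49, Φ(2.46 − 1.96) = 69%.
- 9/8/7/5, two levels (means 8.5 and 6): this removes 1.56 and leaves 4.63, SD 2.15, Φ(2.85 − 1.96) = 81%.

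**Power by simulation, 12 per arm.** This allows for the small sample, so the linear-model figures fall below the approximation.

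| Stage means | Analysis | Stage ignored | Two-level stage used |
|---|---|---|---|
| 10/8/6/4 | log-rank | about 45% | about 66% |
| 10/8/6/4 | linear model | about 48% | about 73% |
| 9/8/7/5 | log-rank | about 63% | about 69% |
| 9/8/7/5 | linear model | – | gain of about 11 points |

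**Type I error.** With no treatment effect, the unadjusted t test rejected in about 5% of simulated trials under both sets of stage means.

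**Wider range.** Other assumed means (10/9/7/5, 12/10/7/4, 13/11/7/3), within-stage SD 2 or 3 and a 2-day benefit put the stage share at 29% to 79%. Simulated power was 15% to 39% with stage ignored and 30% to 59% with all four levels in a linear model. The type I error of the unadjusted test was 4% to 6% throughout. A two-level grouping recovers somewhat less than four levels.

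**The case against.** **Randomisation already protects the test.** Allocation is concealed, 1:1 and blocked, so the unadjusted comparison is unbiased on average and its type I error stays near 5%. This stands. A reader might infer that stage mix can mimic a PDT effect. That is true only as chance imbalance in one realised trial, which the significance level already covers.

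**No effect sought is stated.** A reader might also infer that imbalance shifts the result by about as much as the effect the trial is looking for. The article gives no such effect. Against the assumed 2.5 days, a shift of that size occurs in about 0.4% of trials at 12 per arm. The stronger reading is not supported.

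**The gain depends on the assumptions and the method.** It is large with steep stage differences and modest with flat ones. A four-level linear model gains more than the coarse stratified log-rank test that this sample size allows, so its figures should not be credited to the log-rank test. This stands, and the sizes given for the fix are those of the two-level analyses.

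**Covariates may be left to a fuller document.** This stands for the secondary outcomes. Section 2.14 does not say whether the means are follow-up values or changes, and section 2.12 frames HSV-1 as a decrease after treatment. The article therefore does not show that baseline values go unused. For the primary outcome the objection is weaker, because the article names its comparisons and stage is in neither.

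**Stage is not named as a recorded variable.** Section 2.7 mentions lesion data only in general, and section 2.10 treats each isolated lesion, so one patient could have lesions at different stages. This stands and shapes the fix.

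**Conclusion.** The point holds as one of precision. Time runs from treatment, lesions enter at successive stages, and stage is used neither in randomisation nor in the stated comparisons. Under the assumptions above, using coarse stage adds roughly 6 to 21 points of power with a log-rank test and 11 to 25 with a linear model, at 12 per arm and a 2.5-day benefit. The direction was the same in every scenario tried. The size is uncertain because the article gives only the 15-day upper limit on healing.

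The documents do not support a claim of inflated false positives or systematic bias from stage. This statement concerns the randomised comparison; restricting the analysis to completers is a separate matter.

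The differing stage lists in sections 2 and 2.3 are a plain contradiction that needs no assumptions.

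The secondary outcomes and recurrence would also gain precision from baseline adjustment. That gain cannot be sized from the article, because it depends on correlations and on a spread of recurrence rates that it does not give.

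**What to change.** 1. Reconcile the eligible stages in the opening of section 2 with section 2.3, so that one list applies throughout.
2. State that lesion stage is recorded at T0, with one rule that assigns a single stage to a patient who has several lesions.
3. Name one primary comparison for resolution time: a log-rank test stratified by coarse stage (prodrome/vesicle against ulcer/crust, adapted to the reconciled list), or a Cox model with stage as covariate.
4. Compare VAS, OHIP-14, log HSV-1 and log cytokines by ANCOVA on the baseline value already collected.
5. Adjust the recurrence comparison for the prior-year count from section 2.8.

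**Cost.** No extra patients or visits; slightly more analysis work. The stage grouping must stay coarse because the sample is small. The prior-year count is reported by the patient, which may limit its value. Software other than that named in section 2.14 may be needed.

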### Inclusion and exclusion criteria

2.4

Patients of both sex, with no predilection for race or socioeconomic status, would be included (negative medical history).

Patients with herpes infection in the dry desquamation stage will be excluded. Participants in continuous use of nonsteroidal anti-inflammatory drugs and continued corticosteroid therapy ^[28]^ for <1 week, diabetic participants, smokers who need immunosuppressants, pregnant women and/or nursing mothers, human immunodeficiency virus positive, and hepatitis B or C will be also excluded.

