### Study variables and time

2.12

The primary study variable will be evaluation of the resolution time of the lesions in days (primary objective of the study). For this, a 15-day follow-up will be performed for this variable.

The secondary variables of the study will be

Follow-up of the recurrences of herpes simplex labialis (HSL) lesion at baseline (T0), 1 (T3), 6 months (T4), and 1 year (T5) follow-up periods.Presence of ballooning cells by exfoliative cytology at baseline (T0) and 3 (T1) days after injury.Evaluate if the amount of HSV-1 decreases after treatment with aPDT by Quantitative polymerase chain reaction q at the baseline (T0), 3 (T1), and 7 (T2).Evaluation of cytokines interleukin (IL)-6, IL-1β, IL-8, tumor necrosis factor alpha (TNF-α), and IL-10 by enzyme-linked immunosorbent assay method in nonstimulated saliva and HSL lesions in the baseline (T0), 3 (T1), 7 (T2), and 30 days after treatment (T3).To verify the presence of pain in HSL patients by HSL VAS at baseline (T0), 3 (T1), 7 (T2), and 30 days after treatment (T3).Check the temperature at the site of HSL lesion at baseline (T0), 3 (T1), 7 (T2), and 30 days after treatment (T3).Quality of life perception of HSL patients related to oral health will be assessed using the OHIP-14 questionnaire at baseline (T0) and 30 (T3) days after treatment.

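### Recurrence is part of the stated objective but is left to an unadjusted t test, although the prior-year infection count that would sharpen the comparison is already collected

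*Protocol article*

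**What the plan says.** - **Objective.** The Introduction closes by stating that "the objective of this study will be to evaluate whether PDT is able to reduce the healing time of these lesions and decrease their recurrence".
- **Rank.** Section 2.12 gives healing time first place: "The primary study variable will be evaluation of the resolution time of the lesions in days (primary objective of the study". Recurrence is the first of the secondary variables listed: "Follow-up of the recurrences of herpes simplex labialis (HSL) lesion at baseline (T0), 1 (T3), 6 months (T4), and 1 year (T5) follow-up periods". The Methods also call patients back at each recurrence, so a count over the year can be obtained.
- **Entry.** Section 2.3 reads: "The sample will be composed of healthy patients aged 15 to 60 years who have herpes lesions in the prodromal stage, vesicles, ulcers, and crusts". Section 2.4 reads: "Patients of both sex, with no predilection for race or socioeconomic status, would be included (negative medical history". Neither asks for an earlier episode or a minimum yearly frequency, and neither excludes a first episode. The bracketed remark about medical history sits with the general health criteria and does not shut out people with previous herpes.
- **Baseline information.** Section 2.8: the patient "will be asked when was the first infection and how many infections occurred within 1 year".
- **Allocation.** Section 2.5 uses blocks of 6 and does not stratify by earlier episodes.
- **Analysis.** Section 2.14 applies a t test to every comparison of means and names no covariate. The Kaplan-Meier method in section 2.1 concerns days to recovery, not recurrence.

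**The concern.** How often a patient had herpes in the past year is the natural predictor of how often it returns in the next. The trial asks for that number, admits patients whatever the answer, and then states a comparison that ignores it. Patients who rarely recur dilute the contrast, and the spread between rare and frequent recurrers goes into the error term. With 12 to 15 per arm, a chance difference in underlying frequency could look like prevention by PDT or hide it. Precision on one of the two stated aims is lost although the remedy is already on the case form.

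**Working it through.** **The plan's own figures.** Section 2.1 calculates 24 patients (12 per group), and section 2.5 adds 3 per group for 20% dropout: 12/(1 - 0.2) = 15 per group, 30 in total. That step reproduces. The 24 cannot be reproduced, since no effect size is given, and it concerns days to recovery. No sample size is stated for recurrence.

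**Assumptions.** The document gives no yearly recurrence rate. Assume that each patient has a true yearly rate, gamma-distributed among those enrolled with mean m and SD s, and that episodes in a year are Poisson given that rate. Three cases are used for (m, s): (1, 1), (2, 2) and (2, 1). The last has the least heterogeneity.

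**Value of the prior-year count.** A yearly count has variance m + s², and counts in two years have covariance s². So the correlation is r = s²/(m + s²), and linear adjustment cuts the variance of the between-arm difference by r². With 12 per arm, the SD of that difference is sqrt(2(m + s²)/12) unadjusted, and this is multiplied by sqrt(1 - r²) after adjustment. The equivalent number per arm is 12/(1 - r²).

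| (m, s) | r | Variance cut r² | SD of difference, unadjusted | Adjusted | 12 per arm acts like |
|---|---|---|---|---|---|
| (1, 1) | 1/2 = 0.50 | 25% | sqrt(4/12) = 0.58 | 0.50 | 16 |
| (2, 2) | 4/6 = 0.67 | 44% | sqrt(12/12) = 1.00 | 0.75 | 21.6 |
| (2, 1) | 1/3 = 0.33 | 11% | sqrt(6/12) = 0.71 | 0.67 | 13.5 |

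Fitting the coefficient costs one degree of freedom, so the realised gain is slightly smaller. Counting or not counting the current episode shifts every patient by 1 and leaves r unchanged.

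**Does selection by a visible lesion change this?** Let (m, s) now describe the source population, with gamma shape k = m²/s² and rate b = m/s². If the chance of presenting is proportional to the episode rate, entrants' rates are gamma with shape k + 1 and the same b. Then r = 1/(1 + b) = s²/(m + s²), as before. The 11% to 44% range stands.

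**What an entry rule would add.** Among such entrants, the share with no recurrence in the follow-up year is P0 = (b/(b + 1))^(k+1). With none in either year it is P00 = (b/(b + 2))^(k+1). If at least one prior-year episode were required, the share would be (P0 - P00)/(1 - P0).

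- (1, 1): k = 1, b = 1. P0 = 0.25, P00 = 0.111, and with the rule 0.139/0.75 = 18.5%.
- (2, 2): k = 1, b = 0.5. P0 = 0.111, P00 = 0.04, and with the rule 0.071/0.889 = 8%.

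The rule lowers the share by 6.5 and about 3 percentage points, and turns away about 25% and 11% of presenting patients.

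**Power illustration.** Simulation assumptions: 12 per arm, two-sided 5%, PDT halves the rate, prone patients average 3 episodes a year (gamma shape 2), others 0.1. The t test on follow-up counts has 34% power if all patients are prone and 11% if half are. Linear adjustment for the prior-year count raises these to 44% and 18%. With a mean of 2 among prone patients, and all prone, power goes from 28% to 33%; with a mean of 6, from 43% to 70%.

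**The case against.** **Adjusting a secondary outcome is detail for an analysis plan.** That would be a full answer if the article were silent. It is not: section 2.14 assigns a t test to all comparisons of means. A separate plan that is not shown could use the count, but it would then depart from the stated method.

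**Chance imbalance is generic and is covered by the test's error rate.** This is correct. Allocation is 1:1 and random, so no bias is expected. What remains is lost precision, and here a likely strong predictor is already recorded.

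**Recurrence is secondary.** This also stands. Section 2.12 puts healing time first and section 2.1 sizes the trial on it, so recurrence is part of the stated objective but not its main part.

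**The gain may be modest.** It is 11% in the least heterogeneous case. The count is self-reported, and recall error lowers its correlation with later episodes.

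**A stronger reading is tempting.** From "Recurrence of herpes occurs in 20% to 40% of the world's population", set against the 70% to 80% prevalence in the same section, a reader might infer that many entrants could never show an effect on recurrence. The documents do not support that. Those ranges describe the world population, whereas entrants aged 15 to 60 with an active lesion are enriched for recurrers. No document gives the share of first or rare episodes, and a first-episode patient can still recur within the year.

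**Conclusion.** The point holds as a loss of precision. The trial aims to decrease recurrence, does not select on recurrence history, records the prior-year count, and states a comparison that leaves it out. Adjustment would cut the variance of the recurrence comparison by about 11% to 44%. This rests on assumed gamma-Poisson rates that are stable from year to year and on accurate recall, so the range is illustrative. Even with adjustment, a trial of this size has limited power for recurrence in most of the cases examined.

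A reader might go further and conclude that the entry criteria are wrong, or that the recurrence result would be biased. Neither follows. Once selection by a visible lesion is allowed for, the entry rule gains only about 3 to 6.5 percentage points, and it would also narrow the primary healing-time comparison. Random allocation removes bias on average.

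**What to change.** In sections 2.13.2 and 2.14, replace the unadjusted t test for recurrence with a between-arm comparison of follow-up-year recurrence counts. Use a count model, for example negative binomial, with the prior-year infection count from the anamnesis as a covariate. State in advance how the covariate enters the model and whether the current episode is included in it, so that it is recorded the same way for everyone.

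The cost is a sentence or two. No extra data, visits or patients are needed, and the primary analysis is untouched.

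Limiting entry to patients with recurrent disease is optional. It would align the sample with the recurrence aim, but it slows enrolment and narrows the population for healing time. It is not needed for this correction.
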